## Abstract

**Background:**

Low back pain is a highly prevalent condition in the United States and has a staggeringly negative impact on society in terms of expenses and disability. It has previously been suggested that rehabilitation strategies for persons with recurrent low back pain should be directed to the medial back muscles as these muscles provide functional support of the lumbar region. However, many individuals with low back pain cannot safely and effectively induce trunk muscle adaptation using traditional high-load resistance exercise, and no viable low-load protocols to induce trunk extensor muscle adaptation exist. Herein, we present the study protocol for a randomized controlled trial that will investigate the “cross-transfer” of effects of a novel exercise modality, blood flow restricted exercise, on cross-sectional area (primary outcome), strength and endurance (secondary outcomes) of trunk extensor muscles, as well as the pain, disability, and rate of recurrence of low back pain (tertiary outcomes).

**Methods and study design:**

This is a single-blinded, single-site, randomized controlled trial. A minimum of 32 (and up to 40) subjects aged 18 to 50 years with recurrent low back pain and poor trunk extensor muscle endurance will be recruited, enrolled and randomized. After completion of baseline assessments, participants will be randomized in a 1:1 ratio to receive a 10-week resistance exercise training program with blood flow restriction (BFR exercise group) or without blood flow restriction (control exercise group). Repeat assessments will be taken immediately post intervention and at 12 weeks after the completion of the exercise program. Furthermore, once every 4 weeks during a 36-week follow-up period, participants will be asked to rate their perceived disability and back pain over the past 14 days.

**Discussion:**

This study will examine the potential for blood flow restricted exercise applied to appendicular muscles to result in a “cross-transfer” of therapeutic effect to the lumbar musculature in individuals with low back pain. The results of this study will provide important insights into the effectiveness of this novel exercise modality, which could potentially provide the foundation for a cost-effective and easy-to-implement rehabilitation strategy to induce muscle adaptation in the absence of high mechanical and compressive loading on the spine.

**Trial registration:**

This trial is registered with ClinicalTrials.gov (registration number: NCT02308189, date of registration: 2 December 2014).

## Background

Low back pain (LBP) is a highly prevalent condition in the United States and has a staggeringly negative impact on society in terms of expenses and disability. It is the most common reason for seeking medical care, resulting in more than 52.3 million physician visits annually in 2012 [1]. Ninety percent of adults will experience LBP in their lifetime, and the recurrence of LBP in the year following an acute episode ranges from 24 to 87 % [2]. Acute occurrence of LBP results in rapid onset of atrophy of the lumbar multifidus muscle [3], and patients with both recurrent and chronic LBP exhibit wasting of the trunk extensors (TEs) [4–9]. The TE muscles of patients with recurrent and chronic LBP are also substantially weaker [10–14] and more fatigable [11, 15–20] than those of healthy individuals. Further, TE weakness is predictive of LBP recurrence [21, 22], and poor endurance is predictive of an increased risk for a first-time episode of LBP and recurrence of LBP [21, 23]. Collectively, these findings indicate that persons with LBP, particularly recurrent LBP, exhibit deconditioned TE muscles [24]. Thus, the enhancement of an individual’s level of muscular fitness using exercise interventions has long been an important goal in the rehabilitation of LBP, and it has previously been suggested that rehabilitation strategies for persons with recurrent LBP should be directed to the medial back muscles as these muscles provide functional support of the lumbar region [25].

Indeed, rehabilitation strategies for LBP often attempt to tackle maladaptive changes in TE muscle morphology and function, and they have been shown to be helpful in the management of LBP [26]. However, according to the most recent Cochrane review, exercise therapy is only “somewhat effective” at decreasing LBP and improving function [27]. Exercise therapy encompasses a variety of interventions varying in type, intensity, and frequency. The most common types of LBP exercises are (1) strengthening, (2) stretching, (3) aerobic, (4) coordination, and (5) mobilizing exercises [28, 29]. Among these, strengthening exercises were the most effective for improving function and ranked third for improving LBP [28]. Numerous studies have shown that low- and moderate-load trunk extension resistance exercise increases TE muscle size, strength, and endurance and also reduces pain and disability in recurrent and chronic LBP [30–35]. However, the overall effectiveness of current exercise therapy protocols would be improved if a greater stimulus for adaptation could be provided to the musculature. While the American College of Sports Medicine recommends high-load exercise for inducing muscle adaptation [36], the vast majority of TE exercises for the rehabilitation of LBP [37] are performed at low loads. This assertion is supported by observations that (1) moderate-load trunk extension exercise reduces disability more than low-load exercise, and (2) high-load trunk extension exercise increases erector spinae muscle volume by 2.2 %, whereas low-load exercises do not induce hypertrophy [38]. With this stated, the reasoning for avoiding high-load exercise is rational due to concern over the high mechanical and compressive loading on the spine [37, 39]. Hence, the problem facing clinicians is that many individuals with LBP cannot safely and effectively induce trunk muscle adaptation using traditional high-load resistance exercise, and no viable low-load protocols to induce TE muscle adaptation exist. Taken together, it is crucial to develop therapeutic approaches utilizing low mechanical loads that can still deliver sufficient stimuli to the TE muscles and reverse the changes in TE muscles commonly observed in patients with LBP.

One potential approach to addressing this paradoxical problem is to utilize blood flow restricted (BFR) exercise (also referred to as KAATSU exercise). This involves performing exercise with low loads while blood flow to the working muscles is partially occluded by a pressure cuff. Evidence collected over the past decade suggests that performing low-load exercise with modest BFR to the exercising muscles serves as a potent stimulus for increasing muscle mass [40–47], strength [40–45, 47–54] and endurance [41, 44, 55, 56]. The mechanisms of BFR exercise have begun to be explored. We recently reported the notion that low-load BFR exercise down-regulates proteolytic gene expression [57], and others have observed that it enhances mammalian target of rapamycin signaling and stimulates muscle protein synthesis [58–60]. Additionally, resistance training with BFR amplifies high-energy phosphate depletion, decreases muscle pH, and maintains this altered metabolic milieu [61]. The subsequent strong stimulation of the metaboreflex may explain the findings from numerous studies, including our own, indicating that a single bout of BFR exercise increases serum growth hormone levels [44, 62–64] comparable to, or greater than, that observed during resistance training at much higher intensities [65].

Without question, BFR exercise cannot be directly applied to muscles of the trunk as it is not feasible to occlude circulation of the thorax. However, there is evidence that BFR exercise not only has hypertrophy-promoting effects on the exercising muscles that are undergoing BFR, but also results in systemic hypertrophy-promoting effects that extend to muscles not exercising under BFR conditions. Madarame et al. reported that 10 weeks of low-load leg extension resistance exercise, with BFR performed prior to low-load elbow flexor exercise without BFR, increased muscle strength (9.8 %) and size (12 %) of the elbow flexor muscle group even though the elbow flexors were trained without BFR [66]. While their findings are promising, this “cross-transfer” of effect of BFR exercise has been investigated minimally and thus further research is needed. In particular, determining whether or not blood flow restricted exercise exerts a “cross-transfer” of effect to muscle groups that stabilize the spine is of interest due to their clinical relevance to LBP. Herein, we present the study protocol for a randomized controlled trial that will generate effect sizes on the effects of BFR exercise on TE cross-sectional area (CSA) (primary outcome), strength and endurance (secondary outcomes), as well as the pain, disability, and rate of recurrence of LBP (tertiary outcomes). We hypothesize that BFR exercise, with the appendicular muscles performed prior to low-load TE exercise, will produce systemic effects that enhance TE muscle adaptation in a dose-response manner beyond those seen with only low-load TE exercise. This study is registered on ClinicalTrials.gov as “The Back Exercises to Neutralize Disability (BEND) Pilot Study” (NCT02308189).

## Methods and study design

This is a single-blinded, single-site, randomized controlled trial. It is a two (group) by three (time) repeated measures factorial design. The overall study design is illustrated in Fig. 1.

**Fig. 1 Fig1:**
[figure not shown]
Study design

1. Between 18 and 50 years of age 2. *Answer “yes” to the following questions:* ▪ Have you had two or more episodes of low back pain (LBP) in the past 12 months with at least one of the episodes causing a restriction of work or leisure time activity? 3. Body mass index between 17 and 37 kg/m^2^ 4. With no condition that could limit participation in supervised resistance training exercise based on the Physical Activity Readiness Questionnaire (PAR-Q) 5. Sedentary lifestyle as measured by a classification of “low” or “moderate” levels of physical activity based on scoring criteria of the International Physical Activity Questionnaire (IPAQ) 6. Exhibit low trunk extensor endurance defined as a time to task failure during the modified-Sorensen test of <176 seconds.
Exclusion criteria
1. Participate in progressive resistance exercise within the previous 24 weeks prior to screening 2. Experienced limb amputation (except for toes) and/or any fracture within 24 weeks 3. Have a personal history of the following neurological disorders: Alzheimer’s disease, amyotrophic lateral sclerosis, multiple sclerosis, Parkinson’s disease, or stroke 4. Have a personal history of the following cardiorespiratory disorders: congestive heart failure, myocardial infarction, or peripheral vascular disease 5. Have conditions (e.g., myasthenia gravis, myositis, muscular dystrophy or myopathy, including drug-induced myopathy) leading to muscle loss, muscle weakness, muscle cramps or myalgia 6. Have a personal history of the following musculoskeletal disorders: rheumatoid arthritis, spinal or pathological fractures, scoliosis, spondylolisthesis, avascular necrosis or osteonecrosis, severe osteoarthritis. (Including a history of spinal surgery or a hip arthroplasty). 7. Have a personal history of any of the following conditions or disorders not previously listed: diabetes, fibromyalgia, active cancer, severe obesity (i.e., body mass index greater than 35 kg/m^2^), clinical depression (i.e., subjects who score 24 or higher on the Center for Epidemiology Depression Scale) 8. Have chronic or relapsing/remitting gastrointestinal disorders such as inflammatory bowel diseases, irritable bowel syndrome or gastrointestinal infections within 28 days of screening 9. Have an acute viral or bacterial upper or lower respiratory infection at screening 10. Have moderate or severe chronic obstructive pulmonary disease 11. Report back pain greater than 4 (on a 10- point numerical pain rating scale) at screening 12. Have a leg length discrepancy >3 cm 13. Exhibit abnormal or uncontrolled blood pressure (BP) at the screening visit (i.e., diastolic BP >100 and/or systolic BP >160 mmHg). If taking anti-hypertensive medication, have to be on stable doses of medication for more than 3 months 14. Exhibit abnormal electrocardiogram findings indicative of left ventricular hypertrophy (based on Cornell voltage criteria) at the screening visit 15. Have a current or recent history (within 1 year of screen) of heavy alcohol consumption (men ≥21 drinks/week, 4 drinks/day; women ≥14 drinks/week, 3 drinks/day) or drug abuse 16. Have a current or previous use of any drugs known to influence muscle mass or performance within 24 weeks 17. Report being pregnant, lactating, or that they anticipate becoming pregnant in the next year 18. Report unexplained weight loss over the past month (>10 lbs) 19. Report they have pending litigation related to an episode of LBP or are receiving any type of disability services 20. Use of systemic glucocorticoids within 12 weeks prior to screening 21. Report having received any treatment for LBP by a health care practitioner in the past 6 weeks22. Have contraindications for exposure to a magnetic field

### Randomization and blinding

Participants will be randomized in a 1:1 ratio to receive a 10-week resistance exercise training program with BFR (BFR exercise group) or without BFR (control exercise group). Randomization will be stratified by sex. Because the sample size in each arm is small, permuted-block randomization will be used to ensure equal sample size. Specifically, we will create blocks with varying sizes (i.e., 4–6) within each sex and will permute treatments within each block. Study personnel conducting outcome assessments will remain blinded to group assignment throughout the study. The allocation code and assignment table were generated by a biostatistician (MN). The study participants were enrolled and assigned to the respective interventions by an unblinded project manager (RC).

### Study time line

A table of events for study is illustrated in Table 2. This study will have a screening/baseline assessment period of 21 days, a 10-week exercise training period and a 36-week follow-up period after the last exercise session. Participants will visit Ohio University’s Clinical and Translational Research Unit facilities prior to the intervention for their baseline assessments (detailed below). Following completion of the 10-week exercise intervention, participants will be re-assessed (primary endpoint). Next, participants will enter a 36-week follow-up period during which all outcomes will be assessed 12 weeks (±7 days) after the completion of the exercise program and once every 4 weeks during the follow-up period, they will be contacted via email to log onto a secure web-based survey system where they will be asked to rate their perceived disability (Roland Morris Disability Questionnaire [67]) and back pain (0–10 numerical pain rating scale) over the past 14 days. These data will be used to calculate the rate, duration, pain intensity, and disability of LBP recurrence during the follow-up period.

**Table 2 Tab2:** Schedule of events for all groups

Study procedure	Screen/baseline period		Intervention period					Follow-up		
	Screen visit 1	Baseline visit 2	Visits 3–6^b^	Visits 7–10^b^	Visits 11–14^b^	Visits 15–18^b^	Visits 19–22^b^	Visit 23^a^	Visit 24^a^	Non-visit surveys
Day (window, ± days)	−21 to −1	−21 to −1	1 − 14	15 − 28	29 − 42	43 − 56	57 − 70	71 ± 4	154 ± 7	Once every 4 weeks^c^
Screening/baseline:										
Informed consent	X									
Inclusion/exclusion	X									
Medical history	X									
Weight	X							X	X	
Height and demographics	X									
PAR-Q, IPAQ	X									
Electrocardiogram	X									
Sorensen test	X									
Randomization			X							
Exercise sessions:										
Exercise^d^			X	X	X^d^	X	X			
Efficacy:										
MRI		X						X	X	
DEXA		X						X	X	
Strength		X						X	X	
Endurance		X						X	X	
Pain and disability	X	X	X	X	X	X	X	X	X	X
Treatment acceptability			X	X	X	X	X			

^a^Efficacy outcome measures may be collected in more than one visit if needed and/or preferred. ^b^Exercise training sessions will be performed twice per week with at least 1 day between the exercise sessions. Once every 2 weeks, prior to performing the exercise, the pain, disability, and treatment acceptability outcomes will be assessed (i.e., pain, disability, and treatment acceptability will be quantified on visits 6, 10, 14, 18, and 22). ^c^On days 98, 126, 154, 182, 210, 238, 266, 294, and 322 ± 3 days study participants will be contacted via email to log onto a secure web-based survey system where they will be asked to rate their perceived disability (Roland Morris Disability Questionnaire) and back pain (0 − 10 numerical pain rating scale) over the past 7 days. ^d^One of the exercise training sessions will be replaced by the strength assessment sessions during week 5.

*DEXA* dual-energy X-ray absorptiometry, *IPAQ* International Physical Activity Questionnaire, *MRI* magnetic resonance imaging, *PAR-Q* Physical Activity Readiness Questionnaire

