### Outcome measures

Outcome measures to be assessed at baseline, after the completion of the exercise intervention, and at week 12 of the follow-up period include:*Trunk extensor muscle cross-sectional area (primary outcome):* magnetic resonance imaging (MRI) will be performed with a 0.25-Tesla Musculoskeletal MRI system (Esaote G-Scan Brio, Genoa, Italy) to acquire contiguous transverse T-1 weighted spin echo image slices in the trunk region between L2 and L5, with a slice thickness of 10 mm. To ensure the consistency within/among subjects, the isocenter will be positioned at the midpoint of the L3/L4 intervertebral disc. The number of the slices will vary across participants to cover the region of our interest. Prior to all MRIs subjects will lie supine for at least 15 minutes to minimize the effects of fluid shifts on volumetric calculations. The post-testing MRI scan will be obtained 3 days after the final training session to minimize the effects of exercise-induced fluid shifts. After scanning, images will be transferred to a computer for calculation of CSA. Muscle anatomical CSA will be calculated for (1) the quadratus lumborum, (2) iliocostalis lumborum/longissimus thoracis (these two muscles will be grouped due to the difficulty in defining distinct fascial borders in some subjects), and (3) the multifidus. This calculation will be based on an average of three slices obtained from the center of the respective muscles*Trunk extensor muscle strength (secondary outcome):* participants will perform three maximum isometric TE contractions on a customized lumbar extension dynamometer (MedX; Ocala, FL, USA) at 36° from full extension (additional trials will be provided as needed if subjects continually exert more force with each trial). Each contraction will last approximately 5 seconds with at least a 60-second interval. Muscle strength will be defined as the highest value recorded in any trial. Muscle strength for leg extensors, plantar flexors, and elbow flexors will also be assessed to permit the calculation of the training intensity for the exercise programs. For all strength assessments, time-series torque signals will be collected at 500 Hz by a Biopac MP150 system (Biopac Systems Inc., Santa Barbara, CA, USA)*Trunk extensor muscle endurance (secondary outcome):* participants will perform a sustained, submaximal isometric trunk extension contraction at 20 % of their baseline muscle strength until volitional task failure on a customized lumbar extension dynamometer at 36° from full extension. During this task, the target will be displayed on a computer monitor placed in front of the participant and the time to task failure will be quantified. The time-series torque signal will be collected at 500 Hz by a Biopac MP150 system (Biopac Systems Inc., Santa Barbara, CA, USA)*Pain and perceived disability (tertiary outcomes):* a 0–10 numerical pain rating (NPR) scale will be used to quantify LBP. The Roland Morris Disability Questionnaire, which consists of 24 items related to LBP, will be used to quantify perceived disability [67]. These data will be used to calculate the rate, duration, pain intensity, and disability of LBP recurrence during the follow-up period. To analyze LBP recurrence, we will first define an episode of LBP as a period of pain in the lower back lasting for more than 24 hours, preceded and followed by a period of at least 1 month without LBP. This definition is consistent with that suggested by de Vet and colleagues [68]. We will then compute the rate of LBP recurrence as the number of episodes per quarter, duration as how long on average each episode lasted within each participant, and intensity as the mean and maximum pain/disability scores over the follow-up period as well as during an episode of LBP occurrence

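### As described, the four-weekly surveys cannot yield the recurrence rate and episode duration that the protocol defines, and their recall period is given as both 14 and 7 days

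*Protocol article*

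**What the plan says.** All references are to the protocol article.

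- **Timing.** Study time line: "once every 4 weeks during the follow-up period, they will be contacted via email to log onto a secure web-based survey system". Table 2, footnote c, lists nine survey days from 98 to 322, each ±3 days.
- **Content and recall.** The Abstract says "participants will be asked to rate their perceived disability and back pain over the past 14 days". Study time line agrees: Roland Morris disability and "back pain (0–10 numerical pain rating scale) over the past 14 days". Table 2, footnote c, describes the same surveys with "numerical pain rating scale) over the past 7 days".
- **Use.** Study time line continues: "These data will be used to calculate the rate, duration, pain intensity, and disability of LBP recurrence during the follow-up period". Outcome measures repeats this statement.
- **Episode definition.** Outcome measures will "define an episode of LBP as a period of pain in the lower back lasting for more than 24 hours". It sets a second condition on top of this minimum length, namely that the pain must be "preceded and followed by a period of at least 1 month without LBP". Rate is then a count of episodes per quarter, and duration is each participant's average episode length. Intensity is the mean and maximum score, both over follow-up and within episodes.
- **Analysis.** Statistical analyses compares the groups on these measures with linear mixed-effects models.

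**The concern.** The definition needs near-continuous information: when pain began, when it ended, and whether about 30 days on either side were clear. The described data are one pain score and one disability score every 28 days, with a recall period shorter than the interval between surveys. Part of every cycle is therefore never asked about, and the article names no item on onset, end or number of pain days.

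The group comparison of recurrence rate and duration is at stake. The trial's stated aim is to supply effect sizes for later studies, so a recurrence estimate built on these data could be carried forward although the defined quantity was not measured. Unasked onset and end dates cannot be reliably recovered later, and no choice of model repairs this. The 14- versus 7-day conflict also leaves unclear what the mean and maximum scores refer to.

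**Working it through.** **Schedule (the protocol's own figures).** Training ends on day 70 and follow-up lasts 36 × 7 = 252 days, so the last day is 70 + 252 = 322. At one survey per 28 days, 252 / 28 = 9 surveys. Both agree with footnote c.

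**Coverage on nominal days.** Days asked about = 9 × recall window *w*.
- *w* = 14: 9 × 14 = 126; 126/252 = 50%. Unasked gap per cycle: 28 − 14 = 14 days.
- *w* = 7: 9 × 7 = 63; 63/252 = 25%. Unasked gap per cycle: 28 − 7 = 21 days.

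With the ±3-day windows, successive surveys are 22 to 34 days apart. The gap is then 8–20 days (*w* = 14) or 15–27 days (*w* = 7). It never closes.

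**Pain-free month.** The longest unbroken observed stretch is 14 or 7 days. A clear month on either side of an episode can be assumed but not observed.

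**Duration and the 24-hour criterion.** Take one positive survey between two zero surveys. The pain may have filled the gap before, the window and the gap after, so its maximum length is (28 − *w*) + *w* + (28 − *w*) = 56 − *w*: 42 days for *w* = 14 and 49 days for *w* = 7. The same pattern also fits pain of under 24 hours. The rating does not distinguish these cases.

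**Episodes that touch no recall window (illustration).** The documents give no episode length. Assume a length of *L* days, onset uniform over the 28-day cycle, nominal survey days, and that any pain inside a window is reported. The share missed is (28 − *w* − *L*)/28 in continuous time, or (28 − *w* − *L* + 1)/28 counting whole days.

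| *L* (assumed) | *w* = 14: continuous / whole days | *w* = 7: continuous / whole days |
|---|---|---|
| 3 | 11/28 = 39% / 12/28 = 43% | 18/28 = 64% / 19/28 = 68% |
| 7 | 7/28 = 25% / 8/28 = 29% | 14/28 = 50% / 15/28 = 54% |
| 14 | 0% / 1/28 = 4% | 7/28 = 25% / 8/28 = 29% |

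**Merging of distinct episodes.** Two episodes are separated by a zero survey whenever the pain-free gap contains a whole recall window. On nominal days this is certain once the gap reaches 28 + *w*, which is 42 days (*w* = 14) or 35 days (*w* = 7). Distinct episodes are at least a month apart by definition, so merging is possible only for gaps of about 30–42 or 30–35 days.

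**Clinic visits.** Pain and disability are also assessed at visits 23 and 24. Day 71 is the start of follow-up, and day 154 is already a nominal survey day. These visits do not fill the gaps.

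**The case against.** **Pain, disability and recurrence are tertiary outcomes of a pilot.** This stands and limits the weight of the point. The stated primary goal is to estimate the effect size. Sample size calculation puts the requirement for pain and disability at 41–112 per group, against 16–20 planned, and makes no p-value adjustment because the study is exploratory. No confirmatory recurrence claim depends on these surveys.

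**The survey form is not shown, and an article condenses.** This stands in part. A reader might infer that the form has no onset, end or pain-day items, but the article supports only that none is named. It does, however, say twice that rate and duration come from the named data, and it states a recall shorter than the survey interval. The 14/7-day contradiction stands whatever the form contains.

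**The size of the loss depends on unknown episode lengths.** This is correct, and the table is therefore conditional. A reader might also quote a single range of 25–64%. That would pool two mutually exclusive recall periods. Under 14-day recall, episodes of two weeks or more are almost always touched by a window. The argument about the pain-free month, the 24-hour criterion and duration needs none of these assumptions.

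**Separate episodes would be merged throughout.** A reader might infer this, but it is too strong: merging is confined to the narrow range of gaps derived above.

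**Conclusion.** The mismatch is real and should be fixed. As described, a pain rating and a Roland Morris score every 28 days cannot produce episode rate or duration under the protocol's own definition, because half or three quarters of follow-up is never asked about and no required pain-free month can be observed. The documents also contradict themselves on the recall period.

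The consequences are limited. Mean and maximum pain and disability over the surveyed windows remain computable once one recall period is fixed; intensity within an episode does not, because it depends on identifying the episode. A reader might infer that the trial's main result is compromised. The documents do not support that: cross-sectional area, strength and endurance are measured separately.

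The conclusion rests on the article's description of the survey content. The percentages of missed episodes rest additionally on the assumed 3–7 day lengths, uniform onset and nominal survey days.

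**What to change.** 1. State one recall period for the pain and disability ratings in the Abstract, Study time line and Table 2, footnote c.
2. Unless the form already has them, add items covering all the time since the previous survey (up to 28 + 6 = 34 days given the ±3-day windows): whether any low back pain lasted more than 24 hours, and its start and stop dates or the number of days with pain.
3. State that an episode ending within a month of day 322 cannot meet the condition of a pain-free month afterwards, even with full recall, and treat it as censored.
4. For participants or intervals already surveyed without these items, do not report episode rate or duration. Report mean and maximum scores and the proportion of surveys with low back pain.
5. If the form cannot be changed, replace rate and duration with those measures for everyone.

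**Cost.** An edit to an existing web form with an ethics notification, a slightly longer survey, and more recall error over the longer look-back. Because recruitment is under way, rate and duration may be available for only part of the 32–40 participants.
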